## 8.2 Time schedule

The duration of the study is expected to be approximately 5 months from the beginning of subject recruitment until the final data collection point. Subjects will be scheduled in such a manner that four subjects are tested per day, with a total of 16 per week. Target starting date is October 1 2010.

Timelines from starting date are:

Week Activity

1 - 2 Recruitment and training session subjects 1 - 16

3 - 5 Testing subjects 1 - 16

6 - 7 Recruitment and training session subjects 16 - 32

8 - 10 Testing subjects 16 - 32

11 - 12 Recruitment and training session subjects 32 - 48

13 - 15 Testing subjects 32 – 48

16 - 17 Recruitment and training session subjects 49 - 65

18 - 20 Testing subjects 49 - 65

21 - 25 Database entry and statistical analyses

26 - 29 Report writing

## 8.3 Subject recruitment

Subjects will be recruited by means of posters and advertisements in local newspapers. After volunteers have satisfied the initial inclusion criteria (completed over the telephone), volunteers will be invited to the study site for a training session. During this session, subjects will complete demographics and medical questionnaire, MMSE, and informed consent will be obtained. Baseline blood measure will be obtained during the training session. Volunteers will be enrolled in the study once they have fulfilled all inclusion criteria, present none of the exclusion criteria, and have signed the consent form.

## 8.4 Baseline

Baseline measures will be obtained after a training session (except for blood which will be obtained during the training session) has been completed (V0). Baseline measures will be obtained at the beginning of each testing session and will include the full battery of cognitive tests, subjective mood ratings, brain doppler blood flow.

## 8.5 Visits

**V0 (Training)**

- The investigator will provide information regarding the study procedures, aims, and requirements.
- Medical history and demographics questionnaire will be completed.
- Mini-Mental State Examination (MMSE)
- If all inclusion criteria have been satisfied, informed consent will be obtained.
- Subjects will complete the full battery of cognitive tests and questionnaires to familiarize them with study procedures and minimize procedural learning effects. Specifically:

- Emotional face recognition task

- Jenson Box reaction time task

- Inspection Time task

- Serial sevens

- Serial threes

- N-back task

- Rapid Visual Information Processing task

- Bond and Lader Visual Analogue Scales

- Caffeine Research Visual Analogue Scales

- Blood sample (baseline)

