## 5.2 Subject inclusion criteria

All subjects must comply with all the following inclusion criteria:

- Age 50 and over
- Healthy (i.e. absence of all exclusion criteria) older male and female adults
- Light to moderate coffee drinkers (i.e. with caffeine)
- Drink no more than 16 cups of coffee per week
- Participants must abstain from caffeine-containing foods and beverages, alcohol, no foods containing chlorogenic acids, and only food with low polyphenol content for 24 hours prior to the training session and each testing session.
- Written informed consent obtained

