# Conduct of the trial

## 8.1 Study plan, flow chart

A flow chart of the testing schedule is outlined in Appendix 4.

A short telephone interview will be conducted will all potential subjects to ensure study criteria are met (i.e. see Section 5 Study Population). Successful volunteers will then attend one training session. Note that prior to the training session subjects will be a given a list of foods that need to be avoided prior to the training session. Specifically, subjects will be asked to abstain from caffeine-containing foods and beverages, alcohol, no foods containing chlorogenic acids, and only food with low polyphenol content for 24 hours prior to each testing session. During the training session, subjects will complete demographics and medical questionnaire, the MMSE, and informed consent will be obtained (if criteria are met). Subsequently, subjects will complete the battery of cognitive tests to familiarize subjects with study procedures and minimize procedural learning effects. A baseline blood sample will be obtained.

Approximately 24 hours prior to each testing session, subjects will receive a reminder telephone call that they must abstain from caffeine-containing foods and beverages, alcohol, no foods containing chlorogenic acids, and only food with low polyphenol content for 24 hours prior to each testing session. Subjects are instructed to arrive at the laboratory well rested (following a normal night’s sleep). At the beginning of each experimental session, bread with various spreads and orange juice will be provided. After the participant finishes eating, subjects will complete the mood visual analogue scales followed by the cognitive tests. The mood scales will be completed a second time immediately after baseline cognitive testing is finished. The battery of tests should take approximately 40 minutes to complete. Subsequently, baseline brain doppler blood flow will be obtained. Subjects will then be administered the equivalent of 3 servings of coffee, which must be consumed within 15 minutes.

Based on a previous pharmacokinetic study conducted at Nestlé, following oral ingestion of Nescafé PROTECT coffee, several polyphenol metabolites were shown to peak in plasma within 2 hours after coffee ingestion (Renouf et al., 2008). Based on these results and the results from the acute clinical decaffeinated coffee trial (08.17.NRC), cognitive testing will begin 40 minutes after treatment consumption.

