**4-1 Reporting period**

Serious adverse events require immediate notification to Nestlé or its designated representative beginning from the time that the subject or legal representative provides informed consent which is obtained prior to the subject’s participation in the study, i.e, prior any study related procedure and/or receiving investigational product.

Adverse events should be recorded on the CRF from the time the subject has taken at least one dose of product.

Any serious adverse event occurring any time after the reporting period must be promptly reported if a causal relationship to investigational product is suspected.

Nestlé will be responsible for the reporting of Serious Adverse Events to Regulatory Authorities and to Ethics Committee(s) for clinical trials conducted in the European Community.

However, if required by applicable local regulations, the Investigator, instead of Nestlé, shall notify the Ethics Committee(s) that a serious adverse event has taken place.

Any SAE occurring within 30 days of the last study product administration will be similarly reported by phone or fax within 24 hours and in writing within 3 days of being informed of the event.

In addition, if required by applicable local regulations, the investigator shall promptly notify the Ethics Committee of any SAE brought to his/her attention by the Sponsor and verify the Ethics Committee acknowledges receipt of the information.

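### Sections 8.1 and 8.5 put the medical questionnaire and MMSE before consent and make consent depend on eligibility, whereas Appendix 5 puts consent before any study procedure

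*Protocol*

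**What the plan says.** Section 8.5 lists the V0 steps as study information, then "Medical history and demographics questionnaire will be completed", then the MMSE, and then "If all inclusion criteria have been satisfied, informed consent will be obtained". The cognitive battery, mood scales and baseline blood sample come after that.

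Section 8.1 gives the same order: "During the training session, subjects will complete demographics and medical questionnaire, the MMSE, and informed consent will be obtained (if criteria are met"). It continues: "Subsequently, subjects will complete the battery of cognitive tests to familiarize subjects with study procedures". Section 8.3 names the questionnaire, MMSE and consent in that sequence, and allows enrolment only once the criteria are met and the form is signed.

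The restricted diet begins earlier. Section 5.2 makes it an inclusion criterion "for 24 hours prior to the training session and each testing session", and section 8.1 adds that "prior to the training session subjects will be a given a list of foods that need to be avoided prior to the training session".

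Appendix 5 (4-1) starts the notification period for serious adverse events at informed consent, and describes that consent as obtained "prior any study related procedure and/or receiving investigational product". Section 11.2.2 requires written consent before enrolment and bars treatment without it. Section 11.2.4 adopts the Declaration of Helsinki, reproduced in Appendix 6, under which consent should normally be sought for the collection of identifiable data.

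**The concern.** Two parts of the protocol give different rules on when consent is taken. Sections 8.1 and 8.5 do more than list consent late: they allow it to be sought only from volunteers who have passed screening. Someone who fails the questionnaire or the MMSE has then given medical history and a cognitive score to the study, and under the written sequence is never asked for consent.

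What is at stake is subject protection and consistency with the protocol's own ethical commitments. The endpoint, randomisation, power and analysis are not affected.

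**Working it through.** No arithmetic applies. The check sets the order of steps against the consent rules.

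1. **Order at V0 (section 8.5).** Information, questionnaire, MMSE, consent if eligible, then battery, mood scales and blood sample. Section 8.1 agrees and repeats the condition on eligibility, so the order is not an accident of bullet layout.

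2. **Are the items before consent study procedures?** The MMSE is a defined measure in section 7.4 and an exclusion test in section 5.3 (score below 24). Section 8.10.1 says that demographic and medical data from the training session go into the case report form, and section 8.10.2 sends the original forms to the sponsor's research centre. The diet is imposed by the study through section 5.2, and the V0 requirement is repeated in the session schedule in section 8.1.

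3. **Set against Appendix 5 (4-1).** Consent is to come before any study-related procedure. Three items come before it under sections 5.2, 8.1 and 8.5: the 24-hour diet, the questionnaire and the MMSE.

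4. **Set against section 11.2.2.** Consent before enrolment and before treatment is satisfied by the V0 order. This rule is weaker than the one in Appendix 5 and does not remove the conflict. Section 11.2.2 also places the oral explanation after the investigator has judged the volunteer suitable, whereas section 8.5 puts information first.

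5. **Circularity.** The V0 condition requires all inclusion criteria to be satisfied before consent is obtained. Section 5.2 lists written informed consent among those criteria. Read literally, consent must exist before it can be sought.

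6. **Earlier consent step.** None is described. The telephone interview in section 8.1 checks criteria only.

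7. **What already follows consent.** The cognitive battery, mood scales, blood sample and every study product (first given at V1).

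**The case against.** The strongest defence is that section 11.2.2 governs consent and Appendix 5 mentions its timing only in passing. Appendix 5 also reads like general sponsor text: it refers to trials in the European Community and to a patient's disease, although this trial enrols healthy volunteers in Melbourne. If eligibility screening is not yet participation, sections 8.1, 8.3, 8.5 and 11.2.2 agree with one another. This explains how the mismatch could have arisen but does not resolve it. Appendix 5 itself spells out participation as any study-related procedure, and the MMSE and questionnaire are study measures recorded for the trial.

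The synopsis study plan lists informed consent as the first V0 row, ahead of history and subject data. Row order does not prove sequence, but it shows that the order proposed here fits the protocol. Section 8.3, likewise, joins the three steps in one sentence and does not strictly order them. The explicit order rests on 8.1 and 8.5.

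Three stronger readings are tempting and are not supported:

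- **Blood is drawn or the cognitive battery run without consent.** Sections 8.1 and 8.5 list both after consent.
- **Early procedures run without meaningful safety cover.** The items before consent are a questionnaire, a test that section 7.4 says usually takes under 10 minutes, and a list of foods to avoid. No product is given. Section 10.1 defines an adverse event for a subject given an investigational product, and Appendix 5 records adverse events from the first dose. The gap in serious event reporting is nominal.
- **All 66 enrolled subjects are affected in the same way as screen failures.** Those who pass sign at the same visit, before the battery, blood sample and dosing. The protocol does not say that data from those who fail are kept or analysed.

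It also stands that section 8.5 gives study information before the questionnaire, so volunteers are not uninformed at that point.

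**Conclusion.** The contradiction is real. Sections 8.1 and 8.5 place two screening procedures before consent and make consent conditional on passing them. Appendix 5 says consent comes before any study-related procedure, and the adopted Helsinki text expects consent for collecting identifiable data. The circular condition and the pre-V0 diet are further faults on the same point.

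The practical size is modest. The order applies to every V0 attendee, but the lasting consequence falls on volunteers who fail on site after passing the telephone interview. Their number is not stated and cannot be derived. The procedures concerned are low risk, and no estimate, test or sample size depends on them. The change should still be made, because a written rule on subject protection conflicts with the protocol's own standard and is cheap to correct.

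This rests on two assumptions: that the listed order is the intended order, which the explicit condition supports, and that no consent step before V0 exists outside the document.

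**What to change.** - **Sections 8.1, 8.3 and 8.5:** place written consent directly after the study information and before the questionnaire and MMSE. Make enrolment, not consent, conditional on eligibility; section 8.3 already states the enrolment condition. With consent taken first, its listing in section 5.2 is no longer circular.
- **Section 11.2.2:** align it so that explanation and written consent come before the on-site eligibility assessment.
- **Pre-V0 diet:** reconcile sections 5.2 and 8.1 with Appendix 5. One way is to send the information sheet and obtain documented agreement before the diet starts. Sending the sheet alone would leave the diet before consent. If agreement to the diet is recorded separately from full consent, Appendix 5 should say which of the two starts the reporting period for serious adverse events.

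The visit, its content and the analysis stay as they are. The cost is a few consent forms from volunteers who then fail screening, plus one mailing or contact before V0 if the diet is handled as suggested.

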**V1 (Week 2)**

- Safety assessment recorded in CRF (adverse event record)
- Mood visual analogue scales (Bond-Lader Visual Analogue Scales & Caffeine Research Visual Analogue Scales) will be completed six times (immediately before and after cognitive testing at baseline, 40 minutes and 120 minutes post treatment consumption)
- Cognitive testing will be completed three times (baseline, 40 minutes and 120 minutes post treatment consumption). Specifically:

- Emotional face recognition task

- Jenson Box reaction time task

- Inspection Time task

- Serial sevens

- Serial threes

- N-back task

- Rapid Visual Information Processing task

- Bond and Lader Visual Analogue Scales

- Caffeine Research Visual Analogue Scales

- Blood sample (three times: 10, 90 and 160 minutes post treatment consumption)
- Brain doppler blood flow (baseline and 90 minutes post treatment consumption)

**V2 (Week 3)**

- Safety assessment recorded in CRF (adverse event record)
- Mood visual analogue scales (Bond-Lader Visual Analogue Scales & Caffeine Research Visual Analogue Scales) will be completed six times (immediately before and after cognitive testing at baseline, 40 minutes and 120 minutes post treatment consumption)
- Cognitive testing will be completed three times (baseline, 40 minutes and 120 minutes post treatment consumption). Specifically:

- Emotional face recognition task

- Jenson Box reaction time task

- Inspection Time task

- Serial sevens

- Serial threes

- N-back task

- Rapid Visual Information Processing task

- Bond and Lader Visual Analogue Scales

- Caffeine Research Visual Analogue Scales

- Blood sample (three times: 10, 90 and 160 minutes post treatment consumption)
- Brain doppler blood flow (baseline and 90 minutes post treatment consumption)

**V3 (Week 4)**

- Safety assessment recorded in CRF (adverse event record)
- Mood visual analogue scales (Bond-Lader Visual Analogue Scales & Caffeine Research Visual Analogue Scales) will be completed six times (immediately before and after cognitive testing at baseline, 40 minutes and 120 minutes post treatment consumption)
- Cognitive testing will be completed three times (baseline, 40 minutes and 120 minutes post treatment consumption). Specifically:

- Emotional face recognition task

- Jenson Box reaction time task

- Inspection Time task

- Serial sevens

- Serial threes

- N-back task

- Rapid Visual Information Processing task

- Bond and Lader Visual Analogue Scales

- Caffeine Research Visual Analogue Scales

- Blood sample (three times: 10, 90 and 160 minutes post treatment consumption)
- Brain doppler blood flow (baseline and 90 minutes post treatment consumption)

## 8.6 Final Visit

Final visit is V3

## 8.7 Biological samples

One 7ml blood sample will be obtained during the training session (V0) and three 7ml blood samples will be obtained during each experimental session (V1, V2 and V3). Blood samples will be collected in tube with EDTA as anticoagulant (e.g. Vacutainer BD). Immediately after collection, gently invert the tube eight to ten (8-10) times to evenly mix the blood and anticoagulant. Samples can be kept in fridge or on ice until centrifuging (within 2 hours after collection). Centrifuge the tube at room temperature (at 1600xg for Vacutainer from BD) within 30 minutes of blood collection. Carefully remove the cell-free supernatant plasma without disturbing the cell layer. Transfer the plasma in properly labelled polypropylene test tube by making two aliquots. Store the tubes containing the plasma samples at -20°C or below until shipment on dried ice to NRC. The plasma samples (approx 3ml) will be sent to NRC where analyses will be conducted to assess and compare the bioavailability of various polyphenols found in the pure CGA and the decaffeinated coffee and blood glucose levels.

## 8.8 Follow-up

If any subjects are withdrawn early due to an adverse event, the adverse event protocol will be followed (Appendix 5).

## 8.9 Breaking of the code

The investigator will receive one sealed envelope containing the product identification to be opened only in case of medical emergency.

In circumstances where the investigator identifies an urgent need to break the code, the Clinical Project Manager or the Project Leader should be contacted. All attempts to avoid breaking the code (i.e. withdrawal of treatment) should be made. The code break envelope may be used by the investigator directly in true emergencies. In such cases, the rationale must be documented on the corresponding envelope, with immediate notification of the Clinical Project Manager or the Project Leader.

The code break will also be reported in the subject specific case report form (CRF) and events leading to the emergency breaking will be recorded in the serious adverse event (SAE) report form. All envelopes will be retrieved at the end of the study.

## Data management

### 8.10.1 *Data collection*

Collection mode: paper Case Report Form (CRF)

The CRF will contain all information that is recorded manually, such as the demographic and medical data (medical questionnaires, AEs, SAEs unscheduled visits) which will be collected by the investigator during the training session. The results of the Inspection Time task and the brain doppler blood flow will be recorded directly into the CRF’s.

The complete data set for this study will consist of:

- CRF
- Laboratory data
- Electronic files from cognitive tests. If necessary, the format file, contents and other useful information will be discussed directly with the provider of the data.

The CRF’s are an integral part of this protocol. All data required in the protocol and captured by the investigator will be recorded in the CRFs. The case report forms are made of non-carbon required paper (NCR paper) providing two copies of each page.

All other data should be checked for accuracy versus the subject record.

### *Computerized data entry*

With exception to the Inspection Time task, the Jenson Reaction Time Box task, and the mood visual analogue scales, all cognitive data will be automatically recorded on the computer, and subsequently transferred to a computer database file for statistical analyses. Data for the Inspection Time task and the mood visual analogue scales will also be transferred to the computer database file for statistical analyses.

Data will be entered from the CRFs into a computer database (ClintrialTM 4.6 from Phase Forward – website: [http://www.phaseforward.com](http://www.phaseforward.com/)) at the Nestlé Research Centre (NRC). Upon study completion, all original CRFs will be collected by the CRA/monitor and sent to NRC. Copies of all forms remain at the study site.

### *Computerized edit checks*

The Data Manager will program computerized edit checks at least for data on primary outcome in order to detect discrepancies.

Discrepancies will be treated and if necessary sent to the Investigator on a Data Clarification Form for explanations.

### *Audit trail*

The Clinical Data Management System allows an audit of actions performed by users.

# Statistical aspects and considerations

## 9.1 Background

The primary objective suggested for this trial is to evaluate the effect of acute CGA on attention in terms of performance on the Rapid Visual Information Processing (RVIP) task. In particular, the Total Number of correct Hits, the Reaction Time for the Correct Hits and the False Alarm Rate have been specified. We use the data from a previous trial (08.17.NRC) to estimate the effect sizes and to calculate the sample size needed to have 80% power to detect these effects. In particular, we use the 08.17.NRC data from the Placebo and Decaffeinated Coffee from Green Beans (which is abundant in CGA). The RVIP task consists of identifying targets (sets of 3 consecutive odd/even numbers) out of 96 possible targets. Thus theoretically speaking, this is a binomial trial for each subject with size=96. The success rate is estimated (using data from the placebo group in Trail 08.17.NRC) to be p = 63/96 = .656 which is moderate to large. Thus we expect the data to be fairly Normally distributed. A mixed analysis of covariance (ANCOVA) model was fit to the placebo and decaf coffee from green beans data from the 08.17.NRC trial. The normality and homoscedasticity assumptions were checked. The estimated effect size was an increased score of 2.45 points on the RVIP as compared to placebo and the with-in standard deviation was estimated to be 6.52.

